## Abstract

**Background:**

Brief interventions for smoking cessation and alcohol moderation may contribute considerably to the prevention of cancer among populations at risk, such as cancer survivors, in addition to improving their general wellbeing. There is accumulating evidence for the effectiveness of internet-based brief health behaviour interventions. The objective of this study is to assess the effectiveness, patient-level cost-effectiveness and cost-utility of two new online theory-based self-help interventions among adult cancer survivors in the Netherlands. One of the interventions focuses on alcohol moderation, the other on smoking cessation. Both interventions are tailored to cancer survivors.

**Methods:**

Effectiveness will be assessed in two separate, nearly identical 2-armed RCTs: alcohol moderation (AM RCT) and smoking cessation (SC RCT). Participants are randomly allocated to either the intervention groups or the control groups. In the intervention groups, participants have access to one of the newly developed interventions. In the control groups, participants receive an online static information brochure on alcohol (AM RCT) or smoking (SC RCT). Main study outcome parameters are the number of drinks post-randomisation (AM RCT) and tobacco abstinence (SC RCT). In addition, cost-data and possible effect moderators and mediators will be assessed. Both treatments are internet-based minimally guided self-help interventions: MyCourse – Moderate Drinking (in Dutch: MijnKoers – Minderen met Drinken) and MyCourse – Quit Smoking (MijnKoers – Stoppen met Roken). They are based on cognitive behaviour therapy (CBT), motivational interviewing (MI) and acceptance and commitment therapy (ACT). Both interventions are optimized in collaboration with the target population of cancer survivors in focus groups and interviews, and in collaboration with several experts on eHealth, smoking cessation, alcohol misuse and cancer survivorship.

**Discussion:**

The present study will add to scientific knowledge on the (cost-)effectiveness of internet-based self-help interventions to aid in smoking cessation or alcohol moderation, working mechanisms and impact on quality of life of cancer survivors. If found effective, these interventions can contribute to providing evidence-based psychosocial oncology care to a growing population of cancer survivors.

**Trial registration:**

Trials are prospectively registered in The Netherlands Trial Register (NTR): NTR6011 (SC RCT), NTR6010 (AM RCT) on 1 September 2016.

## Background

In the last decades, milestones have been reached in fighting cancer. For many types of cancer, survival rates after diagnosis have improved. This has led to a lower mortality rate and a larger population of cancer survivors for many types of cancers, especially in developed countries with aging populations, such as the Netherlands [1, 2]. In 2016, 559,170 men and women in the Netherlands had been diagnosed with cancer in the previous 10 years [3] – which is our working definition of a cancer survivor. Projections indicate that this number will rise to 660,000 cancer survivors in the Netherlands in 2020 (with about equal proportions of men and women) [1]. These people are at an increased risk of facing a recurrence of cancer or second cancers [4].

One of the reasons that nowadays second cancers occur more frequently are adverse effects of cancer therapies. However, it is estimated that less than 10% of second cancers occurring among adults can be attributed to radiotherapy [5, 6], while the magnitude of the risk attributable to chemotherapy is very much dependent on the actual class of anti-cancer agent used, and the dose [5]. This suggests that other overall cancer risk factors (i.e. genetic susceptibility, age, environmental factors, lifestyle factors, and combinations of these factors) are important contributors to second cancer risk [5–7].

Smoking, excessive alcohol drinking and excessive bodyweight are among the main preventable risk factors for developing (second) cancers [7, 8], with alcohol and tobacco related cancer sites accounting for 35% of all second cancers [9]. Especially the impact of alcohol as a carcinogen is often underestimated, but like tobacco it contributes considerably to the disease burden from cancers (i.e. [8, 10, 11]). Targeting smoking and excessive alcohol use would not only potentially contribute to preventing second cancers, but also to improving cancer survivors’ quality of life [12, 13]. Cancer survivors are recommended a healthy lifestyle, including a sufficient amount of daily physical activity and healthy diet, without smoking and limited or no alcohol use [14].

Smoking cancer survivors constitute a substantial subgroup of 9.3% of all cancer survivors, and 15% for lung cancer survivors [15]. Most of these current smokers (83%) smoked daily, averaging 14.7 cigarettes per day [15–17]. Alcohol use among cancer survivors does not differ from alcohol use among the general population [18], 6% of the Dutch general population [19] drinks more than the maximum amount of alcohol containing drinks to prevent cancer occurrence (1 glass/day for women, 2 glasses/day for men), as at the time recommended by the World Cancer Research Fund (WCRF) [14]. Several studies report similar results for cancer survivors [20–22]. Male, younger aged head and neck cancer survivors seem to be more likely to engage in risky alcohol use [23]. Based on a total of 660,000 cancer survivors by year 2020, these figures (9.3% smoking and 6% excessively drinking) translate to approximately 61,000 smoking and 39,000 excessively drinking Dutch cancer survivors. For Europe it is estimated that in the year 2020, over 4 million new cancers will be identified; the previous figures imply 383,000 smoking and 247,000 excessively drinking cancer survivors [24]. These cancer survivors could potentially benefit from tailored, evidence-based support to help them quit smoking or limit their alcohol intake.

Based on recent systematic reviews of RCTs among people who smoke or drink excessively, there is accumulating evidence that guided and unguided internet-based interventions for alcohol moderation (AM) [25] and smoking cessation (SC) [26] can be effective, but also leave room for improvement as effect sizes tend to be small. For internet-based alcohol interventions in particular, a recently published meta-analysis, including a total of 16 randomised controlled trials (with 23 comparisons and 5612 participants), showed a small but significant overall effect size in favour of internet interventions, compared to waitlisted participants, information brochures, or assessment only, but this effect is not sustained after 12 months [25]. A paper integrating all recent reviews on this topic came to similar conclusions [27]. In a Cochrane review on internet-based SC interventions, 28 randomised or quasi-randomised trials were included, yielding data from over 45,000 participants. Results were mixed. All in all, internet-based interventions for SC show some positive results for the general population, but leave room for improvement beyond the standard CBT-based internet interventions [26]. A rather new promising therapeutic approach is Acceptance and Commitment Therapy (ACT), part of third-wave CBT. Both therapeutic approaches have shaped the interventions described in this paper, which will be elaborated further in the intervention descriptions.

Although the potential of internet-based interventions to improve lifestyle factors among cancer survivors is recognized [28], most of currently reported interventions target diet and physical exercise [29]. In a recent study, Bantum et al. [30] tested the effectiveness of a six-week Web-based multiple health behaviour change program for adult survivors compared to a waitlist condition in an RCT (*n* = 352). Cancer survivors were eligible if they had completed their primary cancer treatment from 4 weeks to 5 years before enrolment. The web-based intervention positively impacted reduction of insomnia and frequency of exercise [30]. Further, a web-based, tailored SC program for young adult and childhood cancer survivors yielded positive SC outcomes at 15 months post-randomisation in an RCT comparing web and print-based materials. Both versions yielded quit rates (*n* = 374, web-based: 16.5%, print-based: 15.5%) that are similar to the intensive telephone counselling treatment they were based on (15% at 12 months post-randomisation) [31].

Thus far, specific AM and SC internet-based intervention RCTs have not been focused specifically on cancer survivors, with a few exceptions [31, 32]. There is a lack of knowledge on what results in terms of effectiveness and cost-effectiveness could be obtained when existing internet interventions for smoking and alcohol would be tailored to cancer survivors. Based on (Cochrane) reviews on other lifestyle interventions, positive outcomes can be expected [28, 30, 33–35]. Furthermore, time of diagnosis is referred to as a ‘teachable moment’ [36, 37]; cancer diagnosis might trigger cancer survivors and possibly their family members [37] to adapt a more healthy lifestyle and may thus be a good moment to introduce health promotion programs.

The objective of the two RCTs presented in the current study protocol is to test the effectiveness of two newly developed online interventions to reduce alcohol use or tobacco smoking in samples of excessive drinking or smoking cancer survivors.

## Methods

### Aims and hypotheses

The overall aim of the study is to examine the effectiveness and cost-effectiveness of two internet-based interventions for cancer survivors. One intervention focuses on alcohol moderation (AM), the other intervention on smoking cessation (SC). Both interventions will be compared to information-only control groups (CTRL) in a randomised controlled trial (RCT).

It is hypothesized that:The experimental internet-based AM intervention will reduce alcohol use more than CTRL, 6 months post-randomisation.The experimental internet-based AM intervention will show favourable cost-effectiveness (cost per quality-adjusted life year < 20,000 euro) compared to CTRL.The experimental internet-based SC intervention will lead to a higher quit rate than CTRL, 6 months post-randomisation.The experimental internet-based SC intervention will show favourable cost-effectiveness (cost per quality-adjusted life year < 20,000 euro) compared to CTRL.

### Study design

Two separate two-arm RCTs will be carried out (alcohol moderation (AM RCT) and smoking cessation (SC RCT)), each with a follow-up duration of 12 months in an online context. Study design, procedures and measurement instruments of the two RCTs are the same – the main difference is the aim of the intervention (either alcohol moderation or smoking cessation). The RCTs have been designed in line with the CONSORT statement [38]. Both studies are registered in the Dutch Trial Register; identifiers: NTR6010 (AM RCT) and NTR6011 (SC RCT). Ethical approval to carry out the studies was obtained from an accredited medical research and ethics committee in the Netherlands (Toetsingscommissie Wetenschappelijk Onderzoek Rotterdam e.o. NL55921.101.16).

### Study procedure

Applicants meeting inclusion criteria will be informed on the conditions of participation. If they would like to participate, participants are asked for necessary personal data. An invitation email will be sent to them containing the informed consent form, all relevant patient information and a link to register. From this moment on, they have up to 30 days to decide if they want to participate or not. During these 30 days, they can contact a member of the research team responsible for the inclusion process by phone or email or face-to-face for questions regarding the study and interventions. They can also contact an independent physician during these 30 days. After their signed informed consent has been received digitally they are invited to the baseline questionnaire. After they have completed the baseline measurement, randomisation takes place. Depending on the outcome, participants are allocated to one of the two trial arms (active self-help internet-based intervention or passive internet-based information brochure). Participants receive a confirmation email containing a username and instructions how to log in.

Follow-up measurement waves will take place at 3, 6 (primary endpoint), and 12 months post-randomisation (Fig. 1). At each measurement point, participants receive an email including a link to the online questionnaires. Non-respondents receive three reminder emails and are subsequently contacted by telephone in case of continued non-response. As responses are collected online, all data are automatically validated (range checks etc.) on the client side, and after validation stored in a secured server-based database. All data transferred between client and server are encrypted using the Transport Layer Security cryptographic protocol.

**Fig. 1 Fig1:**
[figure not shown]
Flowchart of participant movement in the AM RCT and SC RCT

### Randomisation

After completing the baseline measurement, participants will be allocated to the two trial arms in a 1:1 ratio. As the number of participants we aim to include in each trial arm is not very large, random variation in baseline characteristics could reduce trial arm equivalence. Therefore, allocation through adaptive randomisation (Minimisation [39, 40]) will be used to balance trial arms with regard to age, sex, and education level. Adaptive randomisation implies that the randomisation sequence is not a priori known but is based on the variance in variables that need to be balanced over the trial arms. If imbalance between the trial arms in age, sex or education occurs, the probability of allocation to the trial arm that minimizes this imbalance is increased to 0.67 (instead of 0.5). The randomisation procedure is automatized and performed by triggering a server-sided PHP script using a Mersenne twister random number generator, immediately after the participant has completed the baseline measurement. After randomisation, the participant is informed about the outcome of the randomisation via an automated email, and assigned to one of the two conditions via an automated server-sided computer script. After this assignment, the researchers are informed about the outcome and assignment of the participant via an automated registration in the trial management database. As this is an open label RCT, the participants nor the researchers are blinded regarding the allocated conditions.

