#### Intervention flow

Both interventions are accessible through PC, tablet/iPad and smartphone. Length of the two interventions is equal. Participants are advised to use the intervention for 4 weeks after their set quit/moderation date, but they are free to quit whenever they want. After 4 weeks participants evaluate their goal achievement in the intervention. After this short evaluation all intervention components will remain available for at least 12 months. Table 1 shows descriptions of the main intervention elements, an overview of movement through these elements is shown in Fig. 3.

**Table 1 Tab1:** Main elements within new online interventions MyCourse – Quit Smoking and MyCourse – Moderate Drinking

Main elements	Description
Goal setting	Participants set a quit plan (SC and AM RCT) or moderation plan (only AM RCT) including a quit date
Goal monitoring	Every day participants monitor their drinking or smoking behaviour, mood, cognitions, and contextual cues which have led them to drink or smoke. Feedback is provided in a personalized graph
Exercises based on CBT and ACT	Exercises help identify high risk situations for excessive drinking/smoking and self-management strategies.
	ACT-exercises help accept difficult feelings while keeping focused on the behaviour goal and help exercise self-compassion to prevent relapse
Psycho-education	Effect of alcohol/tobacco on cancer, cancer treatment and life after cancer
Reminders	Several automated email reminders to regularly log on, monitor behaviour and finish all exercises
Peer support platform	A moderated bulletin board, focused on sharing tips and experiences
Social support from social network	Semi-automated email functions throughout the program to send personalized, informing emails to a trusted person

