### Control conditions

The two control-condition interventions provide plain information on risks of alcohol (AM RCT) or smoking (SC RCT) in general and information specifically relevant for cancer survivors. Tips on how to reduce or quit alcohol use or quit smoking are also provided, but do not include the interactive elements that are part of the self-help interventions. Participants in the control groups can access the information page as often as they want by logging in on the website. However, the information on the information pages is static, does not change over time, and is not tailored to the individual participant. After completion of the study, 12 months post-randomisation, these participants are also provided with access to the self-help interventions. All participants are free to seek additional support if needed, use of additional support will be assessed in follow-up measures.

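### The protocol registers every allocation to the research team and does not keep the arm from those who telephone non-respondents or make the remaining analysis choices

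*Protocol article*

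**What the plan says.** **Allocation (Randomisation section).** "The randomisation procedure is automatized and performed by triggering a server-sided PHP script using a Mersenne twister random number generator". The participant learns the result by automated email and is "assigned to one of the two conditions via an automated server-sided computer script". After that, "the researchers are informed about the outcome and assignment of the participant via an automated registration in the trial management database". The section ends: "As this is an open label RCT, the participants nor the researchers are blinded regarding the allocated conditions".

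**Follow-up (Study procedure).** Questionnaires are completed online through an emailed link. "Non-respondents receive three reminder emails and are subsequently contacted by telephone in case of continued non-response". The article does not say who calls, what the caller can see, or what is said.

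**Outcomes (Sample size; Primary measures).** Both primary outcomes are 7-day Timeline Follow-Back self-reports at 6 months: number of drinks in the alcohol trial, abstinence in the smoking trial.

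**Choices left open (Sample size; Statistical analyses).** Sample sizes may be adjusted after a half-way power analysis. Alcohol use may be modelled as a count or as continuous data. Covariates include any variable that differs at baseline with p below .05. At least one further imputation package, not named, will be run beside Amelia 2.

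**Where staff may need the arm.** The abstract states: "Both treatments are internet-based minimally guided self-help interventions". Table 1, under Intervention flow, lists "A moderated bulletin board, focused on sharing tips and experiences". Under Control conditions: "After completion of the study, 12 months post-randomisation, these participants are also provided with access to the self-help interventions".

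**The concern.** Participants cannot be masked to an interactive program versus a static brochure. That does not settle whether follow-up and analysis staff must know the arm. The article gives open-label status as its only reason for leaving researchers unblinded, and it goes further by registering each assignment to them.

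Two things are at stake.

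1. **Follow-up effort.** The telephone step is the only staff contact described in collecting the outcome data. A caller who knows the arm may try harder in one arm than in the other, which changes who is observed in each. If people who respond late differ in outcome from those who respond early, the comparison shifts without any treatment effect.
2. **Analysis choices.** Someone who sees outcomes by named arm while choosing a model, a covariate set, an imputation comparison or a revised sample size can be influenced by the result, even without intent.

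**Working it through.** The document states no figure for this point, so there is none to reproduce. The check sets the passages side by side and adds one labelled illustration.

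**1. Which steps need a person who knows the arm?**

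| Step | Section | Arm needed by staff? |
|---|---|---|
| Randomise, notify, assign | Randomisation | No; scripted |
| Guidance, board moderation | Abstract; Table 1 | Possibly |
| Release of the program to controls at 12 months | Control conditions | Possibly, by whoever administers it |
| Reminder emails, telephone contact | Study procedure | No reason given |
| Range checks on entry | Study procedure | No; automatic |
| Sample-size review, model, covariates, imputation | Sample size; Statistical analyses | Arm names not needed; codes suffice |

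Some roles may need the arm. The article gives no reason why callers or the analyst do.

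**2. How many people does the telephone step concern?** The Sample size section assumes 25% non-response at 6 months, as a maximum in the alcohol trial. Read as what remains missing at that wave, this is 0.25 × 264 = 66 participants (alcohol) and 0.25 × 419 = 104.75, about 105 (smoking). The number telephoned is not given.

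**3. Illustration for the smoking trial, on assumed rates.** Assume no true effect, that the first 60% to respond quit at 16%, and that later responders quit at rate q. With response proportion r, the quit rate among responders is

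(0.60 × 0.16 + (r − 0.60) × q) / r.

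Take q = 6%:

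- r = 0.75: (0.096 + 0.009)/0.75 = 14.0%
- r = 0.70: (0.096 + 0.006)/0.70 = 14.6%
- r = 0.80: (0.096 + 0.012)/0.80 = 13.5%

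Equal response of 75% gives no difference. Response of 70% in one arm and 80% in the other gives 14.57 − 13.50 = 1.07 points.

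Range over q, with the same 70% versus 80%:

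- q = 16% (late responders no different): 16.0 − 16.0 = 0 points
- q = 0%: 0.096/0.70 − 0.096/0.80 = 13.7 − 12.0 = 1.7 points

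A smaller gap, 72.5% versus 77.5%, with q = 6%: 0.1035/0.725 − 0.1065/0.775 = 14.28 − 13.74 = 0.5 points.

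The planned difference is 21 − 10 = 11 points, so these values are at most about a sixth of it (1.7/11 = 0.15). When late responders quit less often, the arm that is chased harder looks worse; the sign reverses if they quit more often. The formula uses raw responder rates, whereas the plan is intention to treat with multiple imputation. Imputation may reduce the distortion, but not fully if late response depends on the unobserved outcome.

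**The case against.** The strongest case against runs as follows. Open-label status is disclosed, and each participant's allocation is revealed only after baseline and randomisation. A journal article normally leaves caller identity, call scripts and attempt limits to the full protocol, and coded-arm analysis to the analysis plan. Answers are entered online and validated automatically, and the emailed link and three reminders are described identically for everyone. The main source of bias, self-report by participants who know their arm, is untouched by masking staff.

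Much of this stands. Nothing here is a contradiction, and the absence of a call script from the article is not itself the point. What remains is what the article states positively: the research team receives every allocation and is unblinded, with no exception for follow-up or analysis.

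A reader might infer more than the document supports:

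- **That the calls are in fact made unmasked.** The caller is not identified. It is likely, because researchers are unblinded and no other caller is named, but it is not stated.
- **That delivery is fully automated, so knowing the arm serves no purpose.** The guidance, the moderated board and the later release to controls may each need someone who knows it.
- **That callers prompt the answers, or that staff hand-code the Timeline Follow-Back data knowing the arm.** Nothing says that answers are taken by telephone, and no manual coding step is described.
- **That the 25% non-response is the group telephoned.** It is an assumed non-response rate at 6 months, not a count of calls.

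**Conclusion.** The concern holds in a limited form. The protocol gives the research team every allocation and provides no protection for two tasks where knowing the arm could matter: chasing non-respondents and settling the analysis choices that remain open. It is a design choice that can be improved cheaply, not an error or a contradiction.

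The size of any bias cannot be computed from the document. The 0 to 1.7 points in the illustration rest wholly on assumed response and quit rates, apply to raw responder rates, and can run either way. They show that unequal chasing alone would probably be modest beside the planned 11 points. The effect of arm-aware analysis choices cannot be put into figures. The conclusion assumes that callers and analysts belong to the research team that the article declares unblinded. If a full protocol already masks them, the Randomisation section should say so.

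**What to change.** In the Randomisation section, replace the general notification of researchers with these provisions:

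1. Allocation is visible only to roles that need it: technical administration, any guidance or board moderation, and release of the program to controls at 12 months.
2. The view used for reminders and telephone follow-up does not show the arm.
3. Callers use one fixed script and the same number of attempts in both arms, and direct participants to the online questionnaire. State who makes the calls.
4. The analyst works with coded arms until the 6-month data are locked. Program-use variables such as logins would reveal the code, so they are kept apart until then.
5. The trial is described as open to participants, with follow-up and analysis staff masked where feasible.

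The cost is a database permission setting and a short call script. Treatment, endpoints and sample size do not change. Two drawbacks remain: some participants will reveal their arm during a call, and questions about the program must be passed to staff with allocation access. Participants' own reporting bias is not addressed by this change and should be acknowledged as a limitation.
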